### Data collection and intervention

#### Demographic and medical survey

The following demographic and medical information will be collected (Table 1): age, sex, smoking history, past and present medical history (e.g., duration of T2DM, hypertension, cardiovascular disease, liver disease, dyslipidemia), diabetes medication and other concomitant medication including steroids and statins during the 12 weeks prior to screening, and frequency of self-monitoring of blood glucose in the recent month.

**Table 1 Tab1:** Study schedule

Study procedure	Screening	Baseline	12 weeks	24 weeks	36 weeks	48 weeks	Early termination
Visit	1	2	3	4	5	6	EDV
Visit window	−28 ~ 0 day	0	±14 days	±14 days	±14 days	±14 days	
Informed consent	**●**						
Demographic information and medical history	**●**						
Inclusion/exclusion criteria	**●**						
Physical examination	**●**						
Randomization		**●**					
Digital integrated healthcare platform application (Groups B, C)		**●**	**●**	**●**	**●**	**●**	**●**
Continuous glucose monitoring system application (Group C)		**●**	**●**	**●**	**●**	**●**	**●**
Continuous glucose monitoring system data collection (Group C)		**●**	**●**	**●**	**●**	**●**	**●**
Vital signs	**●**	**●**	**●**	**●**	**●**	**●**	**●**
Laboratory tests	**●**	**●**	**●**	**●**	**●**	**●**	**●**
Evaluation of hypoglycemia/severe hyperglycemia		**●**	**●**	**●**	**●**	**●**	
Satisfaction questionnaire (DTSQ)	**●**		**●**	**●**	**●**	**●**	**●**
Digital integrated healthcare platform data collection (Group B, C)		**●**	**●**	**●**	**●**	**●**	**●**
Monitoring and intervention (Group C)		**●**	**●**	**●**	**●**	**●**	**●**
Adverse event report		**●**	**●**	**●**	**●**	**●**	**●**
Concomitant drugs	**●**	**●**	**●**	**●**	**●**	**●**	**●**

### Anthropometric and vital sign measurements

At each clinical visit, vital signs including blood pressure, heart rate, and, body weight, and BMI will be collected.

### Laboratory tests

At baseline, week 24, and week 48, blood laboratory tests will be performed after 8 h of fasting. Fasting glucose, HbA1c, total cholesterol, HDL cholesterol, LDL cholesterol, triglycerides, and creatinine will be measured. At weeks 12 and 36, HbA1c and fasting glucose will be measured.

### Distribution and use of at-home measurement devices and the digital integrated healthcare platform

For subjects in experimental groups B and C, at-home measurement devices of a Bluetooth-enabled glucometer, scale with bioelectrical impedance analysis, sphygmomanometer, and watch-type pedometer will be provided. Subjects in group B will configure and apply these devices and the platform by themselves, while subjects in group C will be provided instruction regarding the configuration and use of the devices and the platform by medical staff during their hospital visit.

### Dietary data

For subjects in group B and group C, dietary information will be collected by the AI-based dietary management solution. From a photo of a meal taken prior to eating, the program recognizes the food items. When the subject enters the amount of each food they consume, the dietary information will be converted to food group and calories and recorded on the digital integrated healthcare platform.

### Data acquisition by the digital integrated healthcare platform

For subjects in group C, the following data will be collected from the indicated devices, all Bluetooth-enabled, and recorded on the digital integrated healthcare platform: glucose level from the glucometer; body weight, BMI, and body fat mass measured by a scale with bioelectrical impedance analysis; blood pressure by sphygmomanometer; number of steps, burned calories, and walking distance assessed by a watch-type pedometer; and intake calories assessed by the AI-based dietary management solution. Subjects in group C will be able to access their integrated data via the smartphone app, and medical staff can also access the data on the platform.

### Glucose data by continuous glucose monitoring system

Subjects in group C will apply a CGMS for 1 week prior to the hospital visit at weeks 12, 24, 36, and 48. CGM metrics comprise values of mean glucose; CV; and percentages of time in range (TIR), time above range (TAR), and time below range (TBR) during that week will be collected.

### Evaluation of hypoglycemia and adverse event assessment

At each clinical visit, incidence and frequency of hypoglycemia and severe hypoglycemic events in the previous 3 months will be assessed. Investigators must report all pregnancies or new severe adverse events.

### Questionnaire for satisfaction with diabetes treatment

All subjects will complete the DTSQ to assess the effect of the intervention at every visit.

#### Intervention

Subjects in group A will maintain routine diabetic care during the study period of 48 weeks. Subjects in group B will use a digital integrated healthcare platform by themselves to manage blood glucose during the study period, with no monitoring or intervention from medical staff.

Subjects in group C will be assisted by medical staff in installing the digital integrated healthcare platform when they visit their clinic and will apply the platform during the study period of 48 weeks. Investigators will continuously monitor all data collected from the digital integrated healthcare platform. Medical staff will motivate patients to maintain their self-care through ongoing personal monitoring and intervention. Participants of C group will be provided a copy of the food exchange table on the first day of the study. The daily calorie requirement for each participant is calculated based on the optimal body weight and normal activity level. Each subject in group C will receive a text message once a week via the digital healthcare platform. Clinical registered dietitians will send one of four types of nutritional intervention messages, which are categorized as warning, education, encouragement, or confirmation, based on blood glucose level, CGM metrics, body weight, blood pressure, activity level, and dietary records (Table 2). In addition, a nutritional education message will be sent every 4 weeks.

**Table 2 Tab2:** Contents of interventional text messages

Message type	Examples
Warning	• Warning for excessive calorie intake, extra snacks, high amount of sugar or alcohol consumption. • Lack of daily activity • Imbalance of food intake based on food group: for example, heavy intake of fruit or grains and insufficient intake of protein.
Education	• Card-type mini-educational messages according to the weekly meal pattern; for example, food exchange table, nutrition facts, calories of restaurant food, GI index, and the relationship between exercise and level of blood glucose.
Confirmation	• Verification of previous warning and educational messages • Feedback on daily practice • Instruction and assessment of weekly practice content
Encouragement	• Encouraging message to minimize the drop-out rate • Encouraging message for positive changes in diet or body weight, etc.

A total of four 3-day intensive nutrition management periods are set at 12-week intervals during the 48-week intervention. Participants of C group are encouraged to complete 3-day dietary records and will receive a nutrition management text message every day based on the daily dietary records. The number of educational interventions provided by medical staff at weeks 12, 24, 36, and 48 will be collected.

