### Sample size assumptions

Assuming a 0.3% difference in HbA1c values between the study groups (mean HbA1c 58 mmol/mol (7.44%) [standard deviation, 0.6%]) (effect size d = 0.50) according to previous studies, [7, 11] 78 subjects per group are required, with a two-sided alpha threshold of 0.05 and 80% power. Considering a dropout rate of 20%, the total number of patients required for this study is estimated to be 294 (98 patients per group) from the collective three hospitals.

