### Data analysis

Baseline comparisons between groups for continuous variables will be performed using the two-sample t-test for normally distributed outcomes or Wilcoxon’s rank-sum test for non-normally distributed outcomes. Pearson’s chi-square or Fisher’s exact test will be used for categorical variables. Changes from baseline in each group will be compared by McNemar’s test for proportions and the paired t-test or Wilcoxon signed-rank test for means.

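### Only group C is sent messages meant to lower drop-out, so week-24 HbA1c may be missing unequally by arm; a comparison limited to patients with week-24 data could be modestly biased, in an unknown direction.

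*Protocol article*

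**What the plan says.** In the Intervention section of the protocol article, the weekly messages belong to one arm: "Each subject in group C will receive a text message once a week via the digital healthcare platform". Table 2, which sets out their contents, includes in its Encouragement row "Encouraging message to minimize the drop-out rate". The same section gives group B the platform without staff contact and gives group A routine care. All arms attend visits 12 weeks apart (Study design). No retention contact for A or B is described.

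The Sample size assumptions section uses one dropout rate for all arms: "Considering a dropout rate of 20%, the total number of patients required for this study is estimated to be 294 (98 patients per group".

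For change from baseline, the Data analysis section names, within each group, McNemar's test for proportions and "the paired t-test or Wilcoxon signed-rank test for means". The Discontinuation of subjects section allows a patient to be dropped for not complying with visits and procedures, or for loss to follow-up. HbA1c is measured at weeks 12 and 24 (Laboratory tests), and Table 1 schedules an early termination visit with laboratory tests.

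**The concern.** The primary outcome is change in HbA1c to six months, so each patient's week-24 value matters. If one arm's treatment includes an effort to keep patients from leaving, the chance that this value is observed can depend on the arm. Randomisation then no longer protects a comparison made only among those who have it.

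Suppose group A loses more patients than group C. If the leavers are doing badly, A's remaining patients look better than A as a whole, and C's benefit is understated. If the leavers are well-controlled patients who lose interest, C's benefit is exaggerated. The same holds for C versus B. B versus A is not touched by this mechanism, since neither arm gets the messages.

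An analysis plan can soften the consequence, but it cannot recover HbA1c values that were never taken. Follow-up effort therefore has to be equalised in the conduct of the trial.

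**Working it through.** **The plan's own figure.** The dropout step reproduces: 78 / (1 − 0.20) = 97.5, rounded up to 98 per group, and 3 × 98 = 294. The 78 itself does not follow from the inputs printed beside it: d = 0.50, two-sided 0.05 and 80% power give 63 per group (normal) or 64 (t-test). That is a separate matter and does not bear on this point.

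**Inputs from the article.** Target difference 0.3 points; SD 0.6 points; 98 randomised per arm; one 20% dropout rate.

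**Inputs assumed, because the article gives none.** Dropout by arm of 20%/20%, 25%/15% and 30%/10% (A/C); correlation 0.7 between week-12 and week-24 HbA1c change; log-odds of dropout after week 12 rising by 0.5 to 1.0 per SD of the week-12 value; true C − A difference −0.30.

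**Formula.** In an arm with dropout p, let D be the mean HbA1c change of leavers minus that of stayers. The mean of stayers differs from the mean of all patients by −p × D. The stayers-only C − A difference is therefore off by

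bias = p_A × D_A − p_C × D_C,

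which is (p_A − p_C) × D when the gap is the same in both arms.

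**Results.** Numerical integration of the logistic dropout model gives these week-24 gaps and biases:

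| Dropout A / C | Log-odds per SD | D_A | D_C | Bias |
|---|---|---|---|---|
| 20% / 20% | 0.5 | 0.202 | 0.202 | 0 |
| 20% / 20% | 1.0 | 0.364 | 0.364 | 0 |
| 25% / 15% | 0.5 | 0.201 | 0.203 | 0.25 × 0.201 − 0.15 × 0.203 = 0.020 |
| 25% / 15% | 1.0 | 0.358 | 0.371 | 0.25 × 0.358 − 0.15 × 0.371 = 0.034 |
| 30% / 10% | 0.5 | 0.200 | 0.205 | 0.30 × 0.200 − 0.10 × 0.205 = 0.040 |
| 30% / 10% | 1.0 | 0.354 | 0.381 | 0.30 × 0.354 − 0.10 × 0.381 = 0.068 |

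A simulation of 3,000 trials per setting agrees. Stayers-only estimates were −0.279 to −0.265 at 25%/15% (shift 0.021 to 0.035) and −0.259 to −0.228 at 30%/10% (shift 0.041 to 0.072).

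**Scale.** With 78 per arm the standard error of the difference is 0.6 × √(2/78) = 0.096. The 25%/15% shift is about a fifth to a third of that. Against the 0.3 target it is 7% to 12% (0.020/0.3 to 0.035/0.3); the 30%/10% shift is 13% to 24% (0.040/0.3 to 0.072/0.3).

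**Sensitivity to the gap.** A larger gap between leavers and stayers scales the result directly. With D = 0.6, a 10-point dropout difference gives 0.10 × 0.6 = 0.06 and a 20-point difference gives 0.20 × 0.6 = 0.12. Equal rates are no guarantee either: at 20% in both arms, D = 0.3 in A and 0 in C gives 0.20 × 0.3 = 0.06.

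**What week-12 data can do.** In the same simulation, predicting dropouts' week-24 values from week 12 within arm gave −0.295 to −0.302 in every setting. This is partly built in, because dropout was made to depend only on the week-12 value. It shows what the model can recover when that holds, not that it will hold.

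**The case against.** A reader might infer that the primary analysis is a completers-only comparison and that anyone lost after week 12 is deleted. The article does not say so. Its paired tests are within-group. It names no between-group test of change, no analysis set and no missing-data rule, and the full protocol or analysis plan commonly supplies these. Their absence is not the fault here, and the bias is conditional on such an analysis.

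A reader might also take the Table 2 line as a trial-retention device that should be removed. It may instead mean leaving the platform: the Abstract says staff will encourage continued use of the programme, and the Discussion cites low app use in an earlier trial that found no HbA1c difference. Encouragement may then be part of what group C is meant to test. This stands, and it is why the messages should stay. Disengagement can still become loss from the trial, through the non-compliance ground for dropping a patient.

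Nor do the documents show that A and B get no reminders. A condensed article may leave these out. A common 20% allowance is ordinary planning and contradicts nothing.

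The early termination visit gives some leavers a later HbA1c, but one taken at exit rather than at week 24, and none for patients who simply stop attending.

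Finally, group C has more contact by design (weekly dietitian messages, glucose monitoring, assisted set-up), so rewording one table row would leave most of any difference in retention. This too stands. The remedy has to be equal follow-up effort, not fewer messages for C.

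**Conclusion.** The point holds as a design risk that is worth closing, not as a demonstrated error. The article makes lowering drop-out a purpose of contact that only group C receives and describes nothing equivalent for the other arms. The tests of change it names do nothing about unequal loss.

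The possible shift in C versus A, or C versus B, is about 0.02 to 0.035 points under 25%/15% dropout and 0.04 to 0.07 under an extreme 30%/10%, against a 0.3-point target. These sizes rest wholly on assumed dropout by arm and an assumed link between HbA1c and leaving. The direction is unknown. With equal dropout and the same leaver–stayer gap in both arms the bias is zero. The modest size and small cost make this a change that should be made, not one on which the trial depends.

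**What to change.** 1. **Conduct (Intervention section).** Leave group C's encouragement messages as part of the intervention. Add that the study office sends one identical visit reminder, with no health content, to all three arms before weeks 12, 24, 36 and 48, and that week-24 HbA1c is sought from every randomised patient regardless of platform use. If such reminders already exist, say so.

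2. **Analysis (Data analysis section).** State that the week-24 between-group difference is estimated by assigned group, from a repeated-measures model of HbA1c at weeks 12 and 24 with baseline HbA1c as covariate. Patients lost after week 12 then contribute. The within-group paired tests can stay as description. If the analysis plan already does this, the article needs only a sentence to match.

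3. **Reporting.** Give week-24 retention and reasons for loss by arm, with a sensitivity analysis for dropout that depends on unobserved HbA1c.

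**Cost.** An automated reminder, one model and one sensitivity analysis. A and B would receive neutral reminders that routine care might not include, a slight departure from pure routine care. The model recovers only losses explained by observed values. It adds little for patients lost before week 12, which is why obtaining the week-24 sample comes first.

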### Data analysis

Baseline comparisons between groups for continuous variables will be performed using the two-sample t-test for normally distributed outcomes or Wilcoxon’s rank-sum test for non-normally distributed outcomes. Pearson’s chi-square or Fisher’s exact test will be used for categorical variables. Changes from baseline in each group will be compared by McNemar’s test for proportions and the paired t-test or Wilcoxon signed-rank test for means.

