### Study design

This is a 48-week, open-label, randomized, multicenter clinical trial conducted in three different university-affiliated hospitals in Seoul, Republic of Korea: Samsung Medical Center, Asan Medical Center, and Kyung Hee University Hospital. Subjects with T2DM will be randomly assigned to three groups in a 1:1:1 ratio. The control group “A” will receive routine diabetes care, with hospital visits every 3 months. Subjects in experimental group “B” will be introduced to the digital integrated healthcare platform to use at home without monitoring or assistance from medical staff. Subjects in experimental group “C” will be introduced to and educated on the healthcare platform for use and application at the hospital. Group C, unlike other groups, will also apply a CGMS for 1 week every 3 months. The medical staff will monitor the integrated healthcare data of group C subjects, including body weight, blood glucose, amount of exercise, and diet information, and will provide personal educational feedback via text message once a week. All subjects will visit a hospital at baseline and every 12 weeks thereafter for a total of 48 weeks (i.e., at week 12, 24, 36, and 48) and undergo a physical examination, blood and urine laboratory tests, and a Diabetes Treatment Satisfaction Questionnaire (DTSQ) at every visit. Figure 1 shows an overview of the study.

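### Baseline values of three randomised groups are to be significance-tested with two-sample tests; such tests say little after randomisation, and adjusting the HbA1c comparison for baseline HbA1c would serve better

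*Protocol article*

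**What the plan says.** The Study design section sets up three arms: "Subjects with T2DM will be randomly assigned to three groups in a 1:1:1 ratio". The Data analysis section then plans tests of baseline values. For continuous variables: "Baseline comparisons between groups for continuous variables will be performed using the two-sample t-test for normally distributed outcomes", or Wilcoxon's rank-sum test where the distribution is not normal. For the rest: "Pearson’s chi-square or Fisher’s exact test will be used for categorical variables". Change is handled within arm: "Changes from baseline in each group will be compared by McNemar’s test for proportions and the paired t-test or Wilcoxon signed-rank test for means".

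The section names no three-group test for continuous variables, no choice of pairs and no covariate adjustment. It also does not say that the baseline p-values will be used for anything.

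The sample size section supplies the figures needed to size the issue: "Assuming a 0.3% difference in HbA1c values between the study groups", with "standard deviation, 0.6%]) (effect size d = 0.50", and 98 patients per group after allowance for dropout.

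**The concern.** There are two separate problems.

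First, the t-test and the rank-sum test each compare two groups. With arms A, B and C, someone must choose the pairs, and each extra pair adds a test.

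Second, and more basic, a baseline test in a randomised trial asks whether an observed difference could be due to chance, when sound randomisation already guarantees that it is. A significant result is then a false alarm. A non-significant one does not show that an imbalance in a prognostic variable is negligible. For baseline HbA1c the useful question is how much a chance gap affects the estimated treatment difference, and a p-value does not answer it.

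At stake is how the baseline table is read, and a missed chance to deal with baseline HbA1c in the model whatever its p-value.

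**Working it through.** **Inputs from the article.** Three groups, 1:1:1 (Study design). Target difference 0.3% HbA1c, SD 0.6%, 78 per group before and 98 per group after dropout (Sample size assumptions).

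**Assumptions, not in the article.** Number of baseline variables: 12 to 24, judged from the demographic, vital-sign, laboratory and DTSQ items listed. Correlation between variables: 0 to 0.5. An alternative baseline HbA1c SD of 0.4%, because eligibility limits HbA1c to 7.0–8.5%. Correlation between baseline and week-24 HbA1c: 0.3 to 0.7, with equal variances.

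**The plan's own figure.** 78 / (1 − 0.20) = 97.5, rounded up to 98, and 3 × 98 = 294. Both reproduce. The 78 itself does not follow from d = 0.50, two-sided 0.05 and 80% power: 2 × (1.960 + 0.842)² / 0.50² = 62.8, so 63. That is a separate matter. The calculations below use only the 98.

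**False flags per continuous variable.** Under sound randomisation each pairwise test has a 5% error rate, and pairs that share an arm are correlated.
- B vs A and C vs A only: two normal statistics with correlation 0.5 give P(at least one p < 0.05) = 9.1%.
- All three pairs: P(range of three standard normals > 1.96 × √2) = 12.2%. Simulation gives 12% as well.

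**At least one false flag over k variables.** With independent variables and three pairs this is 1 − (1 − 0.122)^k. The correlated cases are simulated.

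| k | three pairs, correlation 0 | 0.3 | 0.5 | two pairs, correlation 0 | 0.5 |
|---|---|---|---|---|---|
| 12 | 79% | 71% | 61% | 68% | 51% |
| 18 | 90% | 83% | 71% | 82% | 61% |
| 24 | 95% | 90% | 77% | 90% | 68% |

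The expected number of false flags with three pairs is 0.05 × 3 × k = 1.8, 2.7 and 3.6, whatever the correlation. One three-group test per variable would still give 1 − 0.95^k = 46% to 71% for 12 to 24 independent variables. A different test therefore lowers the rate but does not remove the problem.

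**HbA1c gap that escapes a pairwise test.** The smallest significant difference is t(0.975; 194 df) × SD × √(2/98):
- SD 0.6%: 1.972 × 0.6 × 0.1429 = 0.169%, which is 56% of the 0.3% target.
- SD 0.4%: 1.972 × 0.4 × 0.1429 = 0.113%, which is 38% of the target.

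How often that happens (simulated, largest of the three gaps, no pair flagged):
- Gap of at least 0.10%: about 35% of trials at SD 0.6%, about 7% at SD 0.4%.
- Gap of at least 0.15%: about 7% of trials at SD 0.6%, about 0% at SD 0.4%.

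**Gain from adjustment.** With common variance σ² and correlation ρ, the per-patient variance is 2σ²(1 − ρ) for change and σ²(1 − ρ²) for a comparison adjusted for baseline. The ratio is (1 + ρ)/2, that is 0.65 at ρ = 0.3 and 0.85 at ρ = 0.7.

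**The case against.** The strongest reply is that nothing in the article depends on these p-values. The Data analysis section does not use them to judge comparability, choose covariates or trigger adjustment, so dropping them alone changes no estimate, error rate or sample size. That stands, and it is why the point is minor. A reader might infer that the p-values will steer later adjustment; the text does not say so.

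Three further replies also stand in part.
- Two-sample tests are valid for any one pair, and comparing each platform arm with routine care is a natural reading of the Hypotheses section. What is missing is the choice of pairs. Chi-square and Fisher tests handle three groups, so the mismatch concerns continuous variables only.
- A reader might conclude that a false alarm is almost certain. That needs many independent variables and all three pairs. The listed variables are plainly correlated (HbA1c with fasting glucose, weight with BMI), and their number is not given. Likely is as far as the figures go.
- A reader might also conclude that the tests will miss an HbA1c imbalance that matters, or might quote their power against a true baseline difference. Randomisation rules out a true difference, so only observed gaps are relevant, and large unflagged gaps are uncommon. The primary outcome is change from baseline, so a gap does not carry over in full. Under the assumptions above, a fraction 1 − ρ of it does: a 0.17% gap shifts the comparison of change by 0.17 × 0.3 = 0.05% to 0.17 × 0.7 = 0.12%.

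Finally, the model for the primary comparison may be in a statistical analysis plan that is not shown. Its absence is therefore not the criticism here. The criticism is of the baseline testing that the article does state.

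**Conclusion.** The concern holds as a minor point with a nearly free improvement. The article plans baseline significance tests that are uninformative after randomisation, and for continuous variables it names two-group tests in a three-group trial without saying which pairs.

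At least one false flag is likely: 61% to 95% if all three pairs are tested over 12 to 24 variables, or 51% to 90% if only the two comparisons with group A are tested. Both ranges rest on the assumed number of variables and correlations of 0 to 0.5. An HbA1c gap of up to 0.17% (SD 0.6%) or 0.11% (assumed SD 0.4%) would pass as non-significant. The documents do not support saying that such a gap is to be expected, or that a false alarm is certain. Direct harm is small. The real gain comes from adjusting for baseline HbA1c regardless of any baseline test.

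**What to change.** In the Data analysis section, replace the baseline tests with a statement that baseline characteristics will be described for groups A, B and C (mean and SD, median and quartiles, or number and percentage) without significance tests, and that no covariate will be chosen on the basis of a baseline p-value.

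State that the between-group comparison of week-24 HbA1c, or of its change, will use a linear model with baseline HbA1c as a pre-specified covariate. If the statistical analysis plan already does so, a reference to it is enough.

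The cost is wording only. Baseline HbA1c is already collected, and there are fewer tests to run. The one drawback is that some readers expect p-values in a baseline table.

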## Methods

### Hypotheses

Our primary hypothesis is that the integrated healthcare platform user group with or without monitoring and feedback by medical staff will show more improved hemoglobin A1c after 6 months of intervention compared to the routine care group. Our secondary hypothesis is that the healthcare platform user group will show greater improvement in HbA1c after 12 months of intervention, improved glycometabolic parameters (Diabetes Treatment Satisfaction Questionnaire [DTSQ] score, body weight, body fat mass, amount of exercise, dietary information, lipid profile, and CGM metrics), and fewer hypoglycemic events or complications after 6 or 12 months of intervention relative to the routine care group.

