### Outcome variables

The primary outcome will be change in HbA1c from baseline to 6 months after intervention.

The main secondary outcome will be levels of HbA1c and fasting blood glucose at weeks 12, 24, 36, and 48. Other secondary outcomes include lipid profile (i.e., total cholesterol, high-density lipoprotein [HDL] cholesterol, triglycerides, and low-density lipoprotein [LDL] cholesterol) at weeks 24 and 48; the incidence of hypoglycemic events and adverse events at weeks 12, 24, 36, and 48; satisfaction evaluation according to the Diabetes Treatment Satisfaction Questionnaire (DTSQ) [9, 10] at weeks 12, 24, 36, and 48; mean body weight, BMI, and body fat mass for 1 week prior to weeks 12, 24, 36, and 48; mean number of steps, burned calories, and walking distance for 1 month prior to weeks 12, 24, 36, and 48; and mean calorie intake for 3 consecutive days prior to weeks 12, 24, 36, and 48. For experimental group C, secondary outcomes also include CGM metrics, specifically the values of mean glucose; coefficient of variation (CV); and percentages of time in range (TIR), time above range (TAR), and time below range (TBR) for 1 week prior to weeks 12, 24, 36, and 48, and the number of educational interventions by medical staff at weeks 12, 24, 36, and 48.

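### The Data analysis section names only within-group paired tests for change from baseline, which does not match the between-group primary hypothesis on HbA1c

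*Protocol article*

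**What the plan says.** Four sections of the protocol article bear on this.

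- **Hypotheses.** The platform groups, with or without staff feedback, "will show more improved hemoglobin A1c after 6 months of intervention compared to the routine care group".
- **Outcome variables.** "The primary outcome will be change in HbA1c from baseline to 6 months after intervention".
- **Sample size assumptions.** "Assuming a 0.3% difference in HbA1c values between the study groups", with an SD of 0.6% and d = 0.50; on that basis "78 subjects per group are required, with a two-sided alpha threshold of 0.05 and 80% power".
- **Data analysis.** There are three sentences. The first covers baseline: "Baseline comparisons between groups for continuous variables will be performed using the two-sample t-test for normally distributed outcomes", with the rank-sum test as the non-normal alternative. The second: "Pearson’s chi-square or Fisher’s exact test will be used for categorical variables". The third covers follow-up: "Changes from baseline in each group will be compared by McNemar’s test for proportions and the paired t-test or Wilcoxon signed-rank test for means".

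No section of the article names a test that compares change in HbA1c, or HbA1c at week 24, between arms.

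**The concern.** Change in HbA1c is the primary outcome variable, and the one sentence that assigns a test to change from baseline assigns a paired test. McNemar's test, the paired t-test and the signed-rank test all need matched observations. They can show whether group C moved from its own baseline, but not whether C moved further than A.

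The distinction matters in this trial. Patients enter on a recent HbA1c between 53 and 69 mmol/mol, the trial is open-label, and all arms attend every 12 weeks. Selection on a recent value and the effect of taking part could therefore shift HbA1c in every arm, including routine care. A significant paired change in B or C would then say nothing about benefit over A. Nor is finding significance in C and none in A a test of the difference between them.

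**Working it through.** **1. Match each named test to the primary comparison (HbA1c change at 6 months, B or C against A).**

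| Test named in Data analysis | Use stated there | Can it compare arms on HbA1c change? |
|---|---|---|
| Two-sample t, rank-sum | Continuous variables, baseline comparisons | Yes in form, but assigned to baseline only |
| Chi-square, Fisher | Categorical variables | No; HbA1c change is continuous |
| McNemar | Change in proportions, in each group | No; paired and binary |
| Paired t, signed-rank | Change in means, in each group | No; paired, within one group |

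No row supplies the primary comparison.

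**2. What the sample size implies.** The inputs are a difference of 0.3%, SD 0.6%, two-sided alpha 0.05 and 80% power, all from Sample size assumptions.

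- d = 0.3/0.6 = 0.50, as stated.
- Two-sample t-test at two-sided 0.05: 63.8, so 64 per group. This does not reproduce 78.
- The same test at 0.025 (0.05 split over two contrasts): 77.3, so 78 per group. This does reproduce it.
- A three-group ANOVA with evenly spaced means and a maximum difference of 0.5 SD gives 78.1, so 79 and close.
- Dropout: 78/0.8 = 97.5, so 98 per group and 3 × 98 = 294, as stated.

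Both routes that reach or nearly reach 78 are between-group analyses. That the stated alpha of 0.05 does not give 78 for one pairwise test is a separate matter; here it shows only which kind of analysis the number was built for.

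**3. Power of a between-arm test with the planned numbers.** With 78 evaluable per arm and d = 0.50, a two-sample t-test has power 0.873 at two-sided 0.05 and 0.804 at 0.025. This takes 0.6% as the SD of the analysed quantity. The article attaches that SD to an HbA1c level (mean 7.44%) and gives no SD of change.

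**4. Illustration: efficacy judged from separate paired tests.** The article does not state this rule. Assume no true difference between arms, 78 evaluable per arm, an SD of change of 0.6% and the same true fall δ in every arm.

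- p = power of the paired t-test, with noncentrality δ/0.6 × √78.
- P(B or C significant) = 1 − (1 − p)².
- P(B or C significant, A not) = (1 − p) × [1 − (1 − p)²].

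| Common fall δ | p | B or C significant | B or C significant, A not |
|---|---|---|---|
| 0.10% | 0.307 | 52% | 36% |
| 0.15% | 0.587 | 83% | 34% |
| 0.20% | 0.828 | 97% | 17% |

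Between the tabulated falls the last column can rise slightly higher. With q = 1 − p, q(1 − q²) is largest at q = 1/√3, where it equals 2/(3√3) = 38%.

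**Sensitivity to the SD.** If 0.6% is the SD of level and the baseline/follow-up correlation is 0.3, the SD of change is 0.6 × √(2 × 0.7) = 0.71%. A common fall of 0.15% then gives 70% and 38% in place of 83% and 34%. The two uses of 0.6% agree only at a correlation of 0.5.

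**The case against.** The strongest reply is that this is a three-sentence summary in a journal article. The sentence on change is a legitimate description of within-group analysis, it does not say the primary hypothesis will be judged that way, and the between-group model can be left to a fuller plan. The comparative hypothesis and the between-group sample size also show what the authors had in mind.

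Much of this stands. A reader might infer that the trial will never test its primary hypothesis, or cannot answer its primary question. The documents do not support that: intent to compare groups is plain, and an unseen plan may name the test. A reader might also take the 17% to 36% figures as the trial's false-positive rate. They are not, because they need a decision rule that the article never states, an assumed common fall and an assumed SD of change.

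The reply does not remove the point. The article does more than stay silent: it confines two-sample tests of continuous variables to baseline and gives change from baseline to paired tests. The wording about comparing changes in each group is loose, but no reading turns a paired test into a comparison of independent arms.

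Two further points are not part of the error. Pairwise two-sample tests are legitimate in a three-arm trial, and dropping significance tests at baseline is good practice only. A plain two-sample test of change would also cure the mismatch; ANCOVA is the better choice, not the only valid one.

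**Conclusion.** The point holds as a conflict between the stated analysis and the stated hypothesis. It rests on the text and not on any simulated figure. Followed as written, the named tests answer whether each arm changed; the hypothesis and the sample size ask whether the arms differ by 0.3%.

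The conclusion is limited to the article as written. The illustration shows why the difference matters if paired results were ever read as evidence of efficacy: at the three falls examined, a pattern favouring the platform by chance would appear in 17% to 36% of trials with no true difference, on the assumptions set out above.

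The mismatch should be corrected before analysis, because it concerns the primary outcome. The planned sample size need not change to do so, provided 0.6% is a fair SD for the analysed quantity.

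**What to change.** For the primary outcome, replace the sentence on changes from baseline with text such as: *HbA1c at week 24 will be compared between arms by ANCOVA with baseline HbA1c and hospital as covariates. The adjusted differences B−A and C−A will be reported with confidence intervals, each tested at a two-sided alpha of [value].*

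Fill in the alpha explicitly. A level of 0.025 per contrast agrees with 78 per group; if another rule for the two contrasts is chosen, state it.

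Use the same type of model for other continuous outcomes measured in all three arms. Keep the paired tests, labelled as within-group description that carries no conclusion on efficacy. If a fuller analysis plan already names the between-arm test, bring the article's wording into line with it.

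The cost is wording only. HbA1c is already measured in every arm at baseline and at week 24, and hospital is known for every patient, so no added patients, visits or data are needed.
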